**Table 1. Incidence of know complications for neoadjuvant CRT following surgical resection.**

| Complications (n=128)          | Percentage (%) | Citation |
|--------------------------------|----------------|----------|
| Any postoperative complication | 39             | [1]      |
| Any surgical complication      | 23             | [1]      |
| Reoperation                    | 7              | [1]      |

### Null and alternative hypotheses

$H_0$ : Addition of sequential ipilimumab and nivolumab to standard neoadjuvant CRT is not safe and tolerable and/or increase surgical complication rates.

$H_1$ : Addition of sequential ipilimumab and nivolumab to standard neoadjuvant CRT is safe and tolerable and does not increase surgical complication rates.

### Sample size calculation

No formal sample size calculation was performed for this safety, tolerability and feasibility phase 2 study.

The 30:50 randomization ratio is a trade-off between having as much as possible patients in the treatment arm and enough patients in the control arm (standard of care treatment complication rates are well known).

The sample size of 80 is defined by the expected patient numbers available in the planned and financed duration time of the study (based on incidence, inclusion criteria and anticipated patient consent ratios). The primary objective (safety) can be compared to known and published values [1]. A doubling (100% increase) of any surgical complication (23% x 2 = 46%) can be excluded with 49 patients (Power=0.90;  $\alpha$ =0.05).

### Statistical methodology

Interim analyses will be performed after every 10 patients from the treatment arm: Reoperation numbers will be determined and the 95% CI compared to historically known and published ratios [1].

95% CI (Exact binomial test) for complication percentages between 5% and 40% in 2.5 steps and expected case numbers are calculated for n=30 (control group) and n=50 (treatment group) patients (Table 2).

**Table 2. 95% CI for complication percentages and expected case numbers for each treatment group.**

| % | n=30           |                   |                  | n=50           |                   |                  | % change  |
|---|----------------|-------------------|------------------|----------------|-------------------|------------------|-----------------------|
|   | n  | CI low | CI up | n  | CI low | CI up |                       |

[figure not shown]

|      |    |   |    |    |    |    |       |
|------|----|---|----|----|----|----|-------|
| 5    | 2  | 0 | 7  | 3  | 1  | 8  | 166.7 |
| 7.5  | 2  | 0 | 7  | 4  | 1  | 10 | 150.0 |
| 10   | 3  | 1 | 8  | 5  | 2  | 11 | 120.0 |
| 12.5 | 4  | 1 | 9  | 6  | 2  | 12 | 100.0 |
| 15   | 5  | 2 | 10 | 8  | 4  | 15 | 87.5  |
| 17.5 | 5  | 2 | 10 | 9  | 4  | 16 | 77.8  |
| 20   | 6  | 2 | 12 | 10 | 5  | 17 | 70.0  |
| 22.5 | 7  | 3 | 13 | 11 | 6  | 18 | 63.6  |
| 25   | 8  | 4 | 14 | 13 | 7  | 20 | 53.8  |
| 27.5 | 8  | 4 | 14 | 14 | 8  | 21 | 50.0  |
| 30   | 9  | 4 | 15 | 15 | 9  | 22 | 46.7  |
| 32.5 | 10 | 5 | 16 | 16 | 10 | 23 | 43.8  |
| 35   | 11 | 6 | 17 | 18 | 11 | 25 | 38.9  |
| 37.5 | 11 | 6 | 17 | 19 | 12 | 26 | 36.8  |
| 40   | 12 | 7 | 18 | 20 | 13 | 27 | 35.0  |

Expected case numbers for each percentage of complication. Percent change between  $CI_{up}$  and expected case numbers calculated for the treatment group ( $n=50$ ). i.e. 5%: 3 expected  $\rightarrow$  8 observed =  $(8-3)/3 = 166.7\%$  change.

After end of the study the case numbers of each complication will be compared to the corresponding calculated  $CI_{low}$  and  $CI_{up}$  numbers for both groups and further rated. If in both groups the numbers are between these borders,  $H_0$  is rejected and the treatment is considered as safe and tolerable. If the case numbers are above the  $CI_{up}$  border in the treatment group,  $H_0$  will be accepted for this complication and the treatment is considered unsafe. If case numbers for a specific complication are below the corresponding  $CI_{low}$  border in the control group, a new complication percentage with confidence intervals for the treatment group will be calculated using the real case numbers in the control group and the case numbers in the treatment group reassessed. For the complication "reoperation" an assessment after every 10 patients of the treatment group will be performed and if the observed case numbers are above the calculated  $CI_{up}$  border case numbers, the study will be terminated (Table 3).

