**Table 3. Reoperation cutoff values for study termination.**

| $n^1$ | $CI_{up}^2$ |
|-------|-------------|
| 10    | 4           |
| 20    | 5           |
| 30    | 7           |
| 40    | 8           |
| 50    | 10          |

Number of recruited patients in the treatment arm. Corresponding calculated  $CI_{up}$  number of cases for the complication "reoperation" [1]. If the respective case number exceeds the calculated  $CI_{up}$  number, the study will be terminated.

[figure not shown]

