#### 11.4.2 Primary endpoint analysis

Safety and tolerability will be assessed by comparing case numbers for any complication in the treatment arm (n=50) with the calculated 95% upper CI numbers of the calculated percentage of expected numbers of current standard therapy (Table 2). Case numbers in the control arm (n=30) will be used to validate expected numbers from current standard therapy (*i.e.* will be compared to the corresponding 95% CI lower and upper borders).

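### After an early Table 3 stop, the final rule still compares raw reoperation counts with borders for 50 and 30 patients, so it usually does not rate reoperation unsafe

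*Protocol*

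**What the plan says.** The verdict rule stands in the Protocol synopsis, Statistical methodology, in the paragraph after Table 2: "After end of the study the case numbers of each complication will be compared to the corresponding calculated" lower and upper numbers in both groups. If the counts in both groups lie between the borders, H0 "is rejected and the treatment is considered as safe and tolerable". If the treatment count is above its upper border, H0 is accepted for that complication and the treatment counts as unsafe. If a control count is below its lower border, the treatment-arm limits are recalculated from the control data.

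The borders have fixed denominators: "expected case numbers are calculated for n=30 (control group) and n=50 (treatment group) patients (Table 2"). Section 11.4.2 repeats this: "Safety and tolerability will be assessed by comparing case numbers for any complication in the treatment arm (n=50") against Table 2, with the control check tied to n=30.

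The stopping rule uses other denominators. Table 3 sets limits of 4, 5, 7, 8 and 10 reoperations at 10, 20, 30, 40 and 50 treatment-arm patients. Its footnote begins "If the respective case number exceeds the calculated" upper number, and the consequence is termination. Section 11.4.6 says the same. Neither place states a verdict, or different borders, for a study that ends this way.

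**The concern.** Both rules are built on the same published reoperation rate of 7%, but one scales its limit to the patients reached and the other does not. A count that is alarming in 10 or 20 patients is unremarkable against a border meant for 50. The primary objective is safety, so this is the conclusion that matters most. As written, the prespecified rule can fail to rate reoperation unsafe in a trial halted because reoperations were too frequent. The team would then have to set the primary rule aside after seeing the data.

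The control check has a related weakness. A control arm of well under 30 can fall below a 30-patient lower border through size alone, and that triggers the recalculation clause.

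**Working it through.** **Inputs.** Reference rates are 7% (reoperation), 23% (any surgical complication) and 39% (any postoperative complication), from Table 1. The method is the exact binomial 95% CI (synopsis, Statistical methodology) with round half up (section 11.4.7). Allocation is 50:30.

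**Step 1: reproduce Table 3.** Expected count x = round half up(0.07n). Upper limit U = 97.5% quantile of Beta(x+1, n−x). Border = round half up(nU).

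| n | 0.07n | x | nU | Border | Smallest stopping count | Rate |
|---|---|---|---|---|---|---|
| 10 | 0.7 | 1 | 4.45 | 4 | 5 | 50% |
| 20 | 1.4 | 1 | 4.97 | 5 | 6 | 30% |
| 30 | 2.1 | 2 | 6.62 | 7 | 8 | 26.7% |
| 40 | 2.8 | 3 | 8.15 | 8 | 9 | 22.5% |
| 50 | 3.5 | 4 | 9.62 | 10 | 11 | 22% |

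All five limits match the protocol.

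**Step 2: the final reoperation border.** Table 2 has no 7% row. The nearest is "7.5 | 2 | 0 | 7 | 4 | 1 | 10 | 150.0", that is, 0 to 7 in controls and 1 to 10 in the treatment arm. The exact 7% rate gives the same borders (at n=50 the limits are 1.11 and 9.62). The counts 5, 6, 8 and 9 all lie inside 1 to 10. With the 5% row (1 to 8), 9/40 would be unsafe, but 5/10, 6/20 and 8/30 would still lie inside. The 6 to 24 controls expected at such a stop have 0 to 7 reoperations with probability at least 0.9998 at a 7% rate.

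**Step 3: how often this happens.** Looks are at 10, 20, 30, 40 and 50. At each look, add a Binomial(10, p) count to every path not yet stopped, then remove the paths above the Table 3 limit. Patients are independent, outcomes are known at each look, and no cases are added after the stop.

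| True rate | Stop at looks 1-4 | Stop at looks 1-4 with 10 or fewer cases | Share |
|---|---|---|---|
| 7% | 0.34% | 0.33% | 99.6% |
| 14% | 12.1% | 11.8% | 97% |
| 20% | 44.1% | 41.9% | 95% |
| 25% | 72.4% | 67.7% | 94% |

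At 25%, a stop at any look has probability 72.4% + 7.0% = 79.4%. Table 2 gives unsafe for reoperation in only (72.4% − 67.7%) + 7.0% = 11.7%.

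**Step 4: patients still to be operated on.** Add Binomial(m, p) further cases after the stop. As a rough guide to m, 50 treatment patients over about 117 to 130 weeks of planned accrual, times about 16 to 17 weeks to surgery, gives 50/130 × 16 = 6.2 to 50/117 × 17 = 7.3. I take m=7, and m=10 as a higher value.

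| True rate | m=0 | m=7 | m=10 |
|---|---|---|---|
| 14% | 97% | 82% | 74% |
| 20% | 95% | 72% | 61% |
| 25% | 94% | 68% | 55% |

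**Step 5: control arm.** At 20 treated, 20 × 30/50 = 12 controls are expected. The 30-patient lower borders at 23% and 39% are 3 and 7.
- Surgical: P(X ≤ 2; 12, 0.23) = 0.45.
- Any postoperative: P(X ≤ 6; 12, 0.39) = 0.86.
- Reoperation: the lower border is 0, so the clause cannot be triggered.

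**Step 6: after the fix.** At the number of patients reached, the upper borders are those of Table 3, and 5, 6, 8 and 9 all exceed them. For 12 controls the method gives lower borders of 1 (x=3, lower limit 0.66) and 2 (x=5, lower limit 1.82). The chance of falling below them is 0.77^12 = 0.04 and 0.61^12 + 12 × 0.39 × 0.61^11 = 0.02.

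**The case against.** **An overall rating of safe is not shown.** A reader might infer that a trial stopped for reoperations would be declared safe and tolerable as a whole. The text does not support that. The favourable rating may require every complication to lie between both borders. A stop at 10 patients cannot then qualify, because any postoperative complication has a lower treatment border of 13. At 20 patients and a 39% rate, the chance of 13 or more is 1.7%. This objection stands, and it limits the point to reoperation. It does not repair the rule: on that reading an early stop is often neither safe nor unsafe.

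**The word corresponding may mean borders for the actual number.** Table 3 uses similar language, so crossing it could be taken as already giving an unsafe verdict. That is a possible intention. But the synopsis ties the final comparison to Table 2, and section 11.4.2 names n=50. Size-specific borders exist only in Table 3, for one complication in one arm.

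**This may be left to the SAP.** Handling of early termination often is. Here, however, the protocol itself fixes both rules, and they do not fit together.

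**The shares depend on no later cases.** This is correct. The verdict comes after the end of the study and Table 3 counts recruited patients, so Step 4 gives the range.

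**An early stop is unlikely at 7% and would be disclosed.** Both are true: the probability is 0.34%, and the authority and ethics committee must be notified. But a stopping rule is there for rates well above 7%, where stops are common.

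**Conclusion.** The concern holds for the complication reoperation and for stops at 10 to 40 treated patients. Every smallest stopping count lies inside the 50-patient border, so the stated rule does not rate reoperation unsafe, and per complication its favourable condition is met.

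It does not cover every stop. Eleven or more cases, or a stop at 50 patients, is rated unsafe. For true rates of 14% to 25%, the share of early stops affected is 94% to 97% if no cases are added, and about 55% to 82% if 7 to 10 recruited patients still go to surgery. The latter rests on an assumed pipeline, since the protocol gives no figure for it.

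The control-arm effect is secondary. It applies only to the other complications. It shows that recalculation can be triggered by a small control arm alone, not that the resulting verdict would be wrong.

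**What to change.** Add two statements to the synopsis paragraph after Table 2 and to section 11.4.2:

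1. If a Table 3 limit is exceeded, H0 is retained for reoperation and the treatment is rated unsafe for that complication, whatever the Table 2 comparison shows.
2. If fewer than 50 treated or 30 control patients are evaluated, the borders for every complication in both arms are recalculated by the same exact binomial method for the number actually evaluated.

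The first keeps the stop and the verdict in agreement even if patients operated on later change the final count. The second removes the effect of size alone on the control check. The cost is two sentences and a rerun of the existing border calculation. No patients or data are added, and the Table 3 limits stay as they are.

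### The synopsis and section 11.4.2 state the primary safety decision differently, and the synopsis rule gives no verdict for a treatment arm with fewer complications than the lower border

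*Protocol*

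**What the plan says.** **Synopsis, Statistical methodology (text after Table 2).** Counts for each complication are compared with CI_low and CI_up in both arms. Three branches follow.

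- The condition for a favourable verdict reads "If in both groups the numbers are between these borders". When it is met, the null hypothesis "is rejected and the treatment is considered as safe and tolerable".
- If the treatment count is above CI_up, H0 "will be accepted for this complication and the treatment is considered unsafe".
- If the control count is below CI_low, a new reference percentage is calculated from the controls and the treatment arm is reassessed against it.

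**Section 11.4.2, Primary endpoint analysis.** The whole criterion for the treatment arm is this: "Safety and tolerability will be assessed by comparing case numbers for any complication in the treatment arm (n=50) with the calculated 95% upper CI numbers". The control arm is compared with both of its borders, but its counts "will be used to validate expected numbers from current standard therapy". Recalculation is not mentioned.

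**Synopsis, Null and alternative hypotheses.** H1 points one way: adding the two drugs "is safe and tolerable and does not increase surgical complication rates".

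**The concern.** This is the trial's only formal H0/H1 decision, and the two statements of it can part company on the same data. The synopsis branches leave two outcomes uncovered:

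- a treatment count below CI_low while the control count is inside its borders;
- a control count above CI_up while the treatment count is not above its own.

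The first is the most favourable safety result the trial could produce. Section 11.4.2 would pass the treatment arm in that case. In the second case it would still pass the treatment comparison, although it does not say what failed validation by the control arm implies.

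The trial is open-label. If the choice between the two statements is made after the counts are known, the primary conclusion is no longer fully fixed in advance.

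**Working it through.** **Inputs.** Published rates are 39%, 23% and 7% (Table 1). The method is "95% CI (Exact binomial test) for complication percentages between 5% and 40% in 2.5 steps" for n=30 and n=50, with limits rounded half up to whole cases (section 11.4.7). The published rates are not rows of Table 2, so I take the nearest rows as an assumption:

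| Complication | Row | Control (n=30) | Treatment (n=50) |
|---|---|---|---|
| Any postoperative, 39% | 40% | 7 to 18 | 13 to 27 |
| Any surgical, 23% | 22.5% | 3 to 13 | 6 to 18 |
| Reoperation, 7% | 7.5% | 0 to 7 | 1 to 10 |

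**Step 1: reproduce the plan's figures.** Take the rounded expected count, compute the Clopper-Pearson 95% limits, multiply by n and round half up. For the 22.5% row at n=50 the expected count is 11, the limits are 0.1153 and 0.3596, and 50 × these gives 5.76 and 17.98, hence 6 and 18. All 15 rows of Table 2 and all 5 rows of Table 3 reproduce. No border is wrong.

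**Step 2: run outcomes through both statements (any surgical complication).**

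| Treatment | Control | Synopsis | Section 11.4.2 |
|---|---|---|---|
| 6 to 18 | 3 to 13 | safe | within limit |
| 19 or more | 3 to 13 | unsafe | limit exceeded |
| 5 or fewer | 3 to 13 | no verdict | within limit |
| 18 or fewer | 14 or more | no verdict | within limit; consequence of failed validation not stated |
| any | 2 or fewer | recalculate and reassess | recalculation not mentioned |

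**Step 3: size.** T is binomial(50, p_T), C is binomial(30, p_C), the arms are independent, and the borders are read as inclusive (the protocol does not say).

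- Upper limit only: P(T ≤ 18).
- Treatment arm within borders: P(6 ≤ T ≤ 18).
- Direct synopsis condition: P(6 ≤ T ≤ 18) × P(3 ≤ C ≤ 13). With p_C = 23% the second factor is 0.977.

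| True rate in treatment arm (control 23%) | P(T ≤ 5) | P(6 ≤ T ≤ 18) | Both arms within borders | P(T ≤ 18) |
|---|---|---|---|---|
| 23% | 0.016 | 0.972 | 0.972 × 0.977 = 0.950 | 0.988 |
| 17.25% (a quarter lower, assumed) | 0.117 | 0.883 | 0.883 × 0.977 = 0.863 | > 0.999 |
| 11.5% (half, assumed) | 0.479 | 0.521 | 0.521 × 0.977 = 0.509 | > 0.999 |

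These figures exclude the recalculation branch. That branch opens only when C ≤ 2, which has probability 0.019 at 23%, so it can raise the 0.509 to at most 0.509 + 0.019 = 0.528.

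**Step 4: the other two complications.** The probability that the treatment count falls below its lower border, at the published rate, a quarter lower and half:

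- any postoperative complication (border 13): 0.019, 0.259, 0.838;
- reoperation (border 1): 0.93^50 = 0.027, 0.9475^50 = 0.067, 0.965^50 = 0.168.

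**Step 5: sensitivity to the row.** Applying the method directly to 23% at n=50 gives 7 to 19 instead of 6 to 18. A count of 6 would then also be without a verdict, so the gap does not depend on the choice of row.

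**The case against.** The strongest reply is that the intended reading is clear enough. H1 is one-directional, the section headed as the primary endpoint analysis uses only the upper limit, and nothing in the protocol treats few complications as unsafe. A sensible reader would call 5 of 50 safe. This is a fair guide to the intention, but that reader has to supply a branch the synopsis does not contain.

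Four stronger readings are tempting, and the documents do not support them.

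- *A low treatment count fails the safety rule.* The synopsis says if, not only if, and its sole condition for unsafe is a count above CI_up. A low count is unclassified, not failed.
- *The rule works backwards.* It does so only below the benchmark. P(6 ≤ T ≤ 18) rises from 0.10 at a true 46% to 0.86 at 30% and 0.97 at 23%, and only then falls. The rule still guards against harm.
- *Section 11.4.2 forbids the recalculation.* It is silent, and silence is not a contrary rule. The practical question is nevertheless open: 2 of 30 controls would give 3 of 50 expected and move the treatment limit from 18 to 8. The chance of 2 or fewer controls at 23% is 0.019.
- *The probability of a safe verdict is badly damaged.* Large gaps need assumed reductions in complications. The protocol states no expectation that the added drugs reduce surgical complications.

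**Conclusion.** The point holds as an inconsistency and a gap in the primary decision rule. The two statements differ on whether the treatment arm has a lower border, on whether the control arm is part of the condition for rejecting H0, and on whether recalculation is mentioned. The synopsis leaves two outcomes without a verdict, one of them the best possible safety result, and a lower border on the treatment arm conflicts with H1.

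At the published 23% in both arms the difference is 0.988 − 0.950 = 0.038. Of this, 0.016 comes from the treatment arm's lower border and about 0.022 from requiring the control arm inside its borders. It grows to about 0.49 only if the treatment is assumed to halve the rate. These sizes rest on the 22.5% row, inclusive borders, independent arms and the direct condition without recalculation. The textual finding rests on none of them. The reoperation stopping rule (Table 3 and section 11.4.6) uses the upper limit only and is unaffected.

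**What to change.** Put one rule in the synopsis and in section 11.4.2:

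- Judge the treatment arm on CI_up only, and say that any count at or below it, including one below CI_low, meets the criterion.
- Remove the both-groups requirement from the condition for rejecting H0.
- State what follows from a control count above CI_up, for example that the published benchmark is judged not applicable and no verdict is drawn from it.
- Carry the recalculation after a low control count in both places or in neither.
- Say whether a count equal to a border is inside it, and which Table 2 row serves each published rate.

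The cost is wording in the protocol, and in the statistical analysis plan if it repeats the rule. No Table 2 border, stopping rule, sample size or data collection changes.

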| PATIENTS / GROUPS        | 
80 patients, 2 groups (50 treatment arm, 30 control arm)
 
Randomization ratio 30:50
                                                                                                                                                                                                                                                                                                                                                                                                                                                                                                                                                                                                                                                                                                                                                                                                                                                                                                                                                                                                                                                                                  |                   |                                           |                   |                                          |                   |

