### 11.2 Sample size considerations

No formal sample size calculation was performed for this safety, tolerability and feasibility phase 2 study.

Nevertheless, an informal power analysis using published data [1] reveals that an increase of 100% of surgical complications (=46%) can be excluded with 49 patients in the treatment arm (Power=0.90,  $\alpha=0.05$ ), compared to the published 23%).

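### For any surgical complication, the decision rule can declare the treatment safe at counts that do not exclude the doubling to 46% that the plan says 49 patients can exclude

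*Protocol*

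**What the plan says.** The synopsis (Null and alternative hypotheses) sets H0 as the combination being unsafe or raising surgical complication rates. Rejecting H0 is therefore the favourable verdict.

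The sample size text gives one operating property: "A doubling (100% increase) of any surgical complication (23% x 2 = 46%) can be excluded with 49 patients", with power 0.90 and alpha 0.05. Section 11.2 repeats that this "can be excluded with 49 patients in the treatment arm". Neither place names the test or says whether alpha is one-sided or two-sided. The arms are planned as "80 patients, 2 groups (50 treatment arm, 30 control arm".

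The decision rule follows Table 2 in the synopsis. H0 is rejected and the treatment called safe and tolerable "If in both groups the numbers are between these borders". A treatment-arm count above the upper border means unsafe. Section 11.4.2 describes the primary analysis as "comparing case numbers for any complication in the treatment arm (n=50) with the calculated 95% upper CI numbers" expected under standard therapy, and uses the lower and upper borders only to validate the control arm. Table 1 gives 23% for any surgical complication. Table 2 runs in steps of 2.5 percentage points and so has rows for 22.5% and 25% but none for 23%.

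**The concern.** The borders describe which counts are compatible with the historical rate. A count inside them shows that the trial has not demonstrated an increase. It does not show that a harmful increase has been ruled out. With H0 defined as not safe, rejection should require the second, but the rule asks only for the first.

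The 46% limit, the only harmful rate the plan names, does not enter the rule. The trial could therefore report its primary conclusion of safety on data that leave a doubling of surgical complications inside the confidence interval. A reader who has seen the sample size text would believe that such a doubling had been excluded.

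**Working it through.** **Inputs.** Historical rate 23% (Table 1); rate to be excluded 2 × 23% = 46%, power 0.90, alpha 0.05 (synopsis, Sample size calculation; section 11.2); treatment arm n = 50 (synopsis); exact binomial intervals with round-half-up (section 11.4.7). X is the number of treatment-arm patients with the complication.

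**1. The plan's figure of 49.** Take the exact test of p = 0.46 with 0.025 in the lower tail (two-sided 0.05).
- n = 49: P(X ≤ 15 | 0.46) = 0.0206 and P(X ≤ 16 | 0.46) = 0.0405, so the test rejects at 15 or fewer. Power at 23% is P(X ≤ 15 | 0.23) = 0.921.
- n = 48: P(X ≤ 15 | 0.46) = 0.0271, so the limit drops to 14 and power is 0.88.

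The 49 reproduces as the smallest size from which power stays at or above 0.90.

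**2. The plan's borders.** Expected count = rate × 50, rounded. Borders = exact 95% limits of that count over 50, times 50, rounded.
- 22.5%: 11.25 → 11; limits 11.53% and 35.96%; borders 5.76 → 6 and 17.98 → 18. This matches Table 2, and all 15 rows reproduce this way.
- 23% by the same method: 11.5 → 12; limits 13.06% and 38.17%; borders 6.53 → 7 and 19.08 → 19.
- 25%: Table 2 gives an upper border of 20.

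**3. What the data exclude near the border (n = 50).**

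| Count | Two-sided 95% upper limit | One-sided 95% upper limit | Within border of 18 | Excludes 46% |
|---|---|---|---|---|
| 15 | 44.6% | 42.4% | yes | yes, both |
| 16 | 46.7% | 44.5% | yes | one-sided only |
| 17 | 48.8% | 46.5% | yes | no |
| 18 | 50.8% | 48.6% | yes | no |

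Counts of 16 to 18 (two-sided) or 17 to 18 (one-sided) are called safe without excluding 46%. With Wilson limits, 18 still fails (49.9% two-sided, 47.6% one-sided).

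**4. Chance of passing the treatment-arm border, P(X ≤ border).**
- True rate 46%: 0.100 (border 18), 0.160 (19), 0.240 (20).
- True rate 34.5% (1.5 × 23%): 0.650 (border 18).
- True rate 23%: 0.988 (border 18); 0.972 if the count must also be at least 6.

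The control-arm condition changes little. A control count lies within 3 to 13 with probability 0.977 at 23%, so 0.100 becomes 0.100 × 0.977 = 0.098.

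**The case against.** The strongest reply is that the quoted power does describe the applied rule. At n = 50 the chance of exceeding 18 when the true rate is 46% is 1 − 0.100 = 0.900. The border of 18 is also the cutoff of an exact two-sided 0.05 test for an increase over 23%: P(X ≥ 19 | 0.23) = 1 − 0.988 = 0.012, and P(X ≥ 18 | 0.23) = 1 − 0.974 = 0.026, which is above 0.025. On this reading, power means detecting harm, and the rule flags a true doubling about nine times in ten.

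This stands in part. A reader might infer that the 0.90 belongs only to another test, but the plan names no test and both fit. Only the test that excludes 46% matches the stated H0 and the claim that a doubling can be excluded. With H0 as not safe, alpha limits the false declaration of safety, and that error is 10.0%, not 5%.

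It is also fair that the plan disclaims a formal sample size calculation and calls its power analysis informal. It nevertheless fixes hypotheses, a rejection rule and a binary verdict on the primary objective.

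If 'between' is read strictly, 17 is the highest passing count. The false-safe chance is then 5.8%, and 17 still fails both exact limits, although the one-sided Wilson limit (45.6%) would clear 46%.

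Two further inferences go beyond the documents:
- **Reoperation.** The plan makes no claim to exclude a doubling of reoperation, and that endpoint is also checked after every 10 treatment-arm patients. Its final limit alone does not describe its behaviour.
- **Low counts.** A reader might infer that an arm with very few complications would be denied the safe verdict. The synopsis wording allows this, but section 11.4.2 compares the treatment arm only with the upper border. The two texts need aligning; a failure rate should not be built on the literal synopsis wording.

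**Conclusion.** The point holds for any surgical complication. The rule rejects a null of not safe on evidence of compatibility with the historical rate. On the 22.5% row, the top two or three passing counts leave the doubling unexcluded, depending on the sidedness of alpha. A true rate of 46% passes in 10.0% of trials, or in 16.0% or 24.0% with a border of 19 or 20. The plan does not say which border applies.

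The figure of 49 is correct as a test of 46%, and a doubled rate would still usually be flagged. The fault is the mismatch between H0, the exclusion claim and the rule.

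This assumes that 46% is the rate to exclude, that alpha 0.05 is meant to limit the false-safe error, and that all 50 treatment-arm patients are evaluable. The sidedness of alpha is not stated, but the conclusion is the same either way.

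**What to change.** In the synopsis rule after Table 2 and in section 11.4.2, for any surgical complication, reject H0 only if the upper exact confidence limit of the observed treatment-arm rate is below 46%. State the sidedness:
- Two-sided 95%: at most 15 of 50; false-safe probability 1.6%; power at 23% 90.7%.
- One-sided 95%: at most 16 of 50; false-safe probability 3.1%; power at 23% 94.9%.

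Apply the criterion to the number actually evaluable (two-sided: 15 of 49, 14 of 48). Because the criterion uses the observed rate, no row of Table 2 has to be chosen. Align the synopsis with section 11.4.2 so that no lower border applies to the treatment arm. For the other complications, for which the plan names no rate to exclude, report the rate with its exact CI and draw no safe verdict from the border.

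Cost: no additional patients. The chance of meeting the treatment-arm criterion at a true 23% falls from 98.8% (upper border of 18 only; 97.2% with borders 6 to 18) to 90.7% or 94.9%. Adopting 46% as the formal limit is the sponsor's decision. It changes the primary decision rule, so it needs a protocol amendment under section 13.2.1.
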